##### Secondary endpoint

The following 3 secondary endpoints will be compared between BCM and control arms using grouped t-test, and within group trend will also be analyzed: (1) left ventricular thickness and left ventricular ejection fraction, (2) pre-HD and post-HD blood pressure, (3) anti-hypertensive medication.

The secondary endpoint of incident rate of hospitalization will be compared between BCM arm and control arm using general Linear Model with Poisson regression.

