## Methods

### Study design

This is an open label, multicenter, prospective, randomized controlled trial. The aim of the study is to assess if BIS guided fluid management can improve long term outcome in MHD patients. Body composition and hydration state will be assessed with a portable whole body bioimpedance spectroscopy device (BCM—Fresenius Medical Care D GmbH). The study will involve 16 clinical sites, enrolling more than 1300 participants. The enrolment period will last approximately 6 months, with a planned minimum 36 months follow-up period. Participants will be randomized to two arms, the control arm and BCM arm. Patients in both arms will receive BCM measurement, but results from the BCM measurement in the control group will be kept blinded to the investigators. Participants in control group will be followed up and their dry weights will be adjusted according to the dialysis center’s standard clinical practice. Clinicians managing participants in the BCM group, in addition to routine practice, will receive BCM measurement and dry weight will be adjusted according to BCM output data estimating overhydration and dry weight. All of baseline demographics, clinical data, laboratory data, regular BCM measurement, and ultrasonic cardiograph (UCG) data will be recorded on study case report forms (CRFs).

The flow chart of the study is shown in Figure
1.

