#### Data collection

Summary of data collection is listed in Table
1.

**Table 1 T1:** BOCOMO study schedule of data collection

**Item**	**Baseline frequency**	**Follow up frequency**
Demographic information	Once	-
ESRD history^1^	Once	-
Comorbidity^2^	Once	-
Physical examination^3^	Once	Every 2 months
Timed urine collection^4^	Once	Every 2 months
CBC^5^	Once	Every 3 months
Routine laboratory data^6^	Once	Every 3 months
Kt/V	Once	Every 3 months
iPTH	Once	Every 3 months
hsCRP	Once	Every 3 months
UCG	Once	Every 12 months
BCM measurement	Once	Every 2 months in BCM arm
Dialysis prescription change^7^	Once	Throughout the study period
Medication change^8^	Once	Throughout the study period
New clinical event^9^	-	Throughout the study period

Abbreviation: BOCOMO study, body composition monitor study; ESRD, end stage renal disease; CBC, complete blood count; Kt/V, calculated using Daugirdas single pool equation; iPTH, intact parathyroid hormone; hsCRP, high sensitive C-reactive protein; UCG, ultrasonic cardiograph.

^1^ESRD history includes cause of ESRD, date of first dialysis, type of vascular access.

^2^Detailed history of comorbidity will be assessed, including vascular access events.

^3^Physical examination includes body weight, blood pressure, heart rate, edema, pulmonary rale, before and after hemodialysis session.

^4^24 hours urine volume collected the day before dialysis session will be recorded.

^5^Consists of hemoglobin, white blood cell count, platelet count.

^6^Consists of albumin, pre-Albumin, creatinine, urea, potassium, sodium, chloride, calcium, phosphate, bicarbonate, alkaline phosphatase (ALP), glucose, triglycerides, total cholesterol, low density lipoprotein, high density lipoprotein, brain natriuretic peptide (BNP).

^7^Any dialysis prescription change throughout the study period will be recorded.

^8^Any medication change throughout the study period will be recorded.

^9^Any new clinical event throughout the study period will be recorded, including hospitalization, new diagnosis, vascular access related event, treatment of abnormal laboratory value, dry weight adjustment.

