##### Baseline data collection

In brief, baseline data are collected before initiation of BCM monitoring and include demographics, ESRD treatment history, current vascular access type, detailed comorbid conditions assessment, current dialysis prescription and medications (oral, subcutaneous and intravenous), CBC, routine laboratory data, Kt/V, iPTH and hsCRP. UCG will also be performed. BCM measurement will be done in participants in both BCM arm and control arm. In the control arm, BCM data will not be provided to patient care provider. 24 hours urine volume will be recorded the day before dialysis session. A physical examination will be performed.

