##### Follow up data collection

Physical examination and urine volume collection will be performed every 2 months. CBC, routine laboratory data, and Kt/V will be obtained every 3 months. iPTH and hsCRP will be measured every 3 months. UCG will be performed every 12 months.

BCM measurement will be performed every 2 months in BCM arm, data will be recorded and provided to the care provider.

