### Statistical analysis

#### Study hypotheses

This study is designed to test the primary hypotheses that patients receiving BCM guided fluid management have lower rate for the composite endpoint of mortality, cardiovascular and cerebrovascular events compared with patients receiving fluid management according to clinical site’s standard care. The secondary hypotheses that will be tested are that patients receiving BCM measurement have (1) lower left ventricular thickness and higher left ventricular ejection fraction, (2) better blood pressure control, (3) less anti-hypertensive medication, (4) lower hospitalization rate.

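### The grouped t-test for the left ventricular, blood pressure and medication endpoints gives up precision that the scheduled baseline and repeat measurements could supply

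*Protocol article*

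**What the plan says.** The protocol article (Analytical method, Secondary endpoint) fixes the method: "The following 3 secondary endpoints will be compared between BCM and control arms using grouped t-test, and within group trend will also be analyzed". The three endpoints are left ventricular thickness with ejection fraction, blood pressure before and after dialysis, and antihypertensive medication. Hospitalization has its own Poisson model. The only covariate-adjusted model apart from that is the Cox model under Primary endpoint.

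The schedule supplies more than one value per patient:

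- Echocardiography at baseline (Baseline data collection: "UCG will also be performed") and then yearly (Follow up data collection: "UCG will be performed every 12 months").
- Blood pressure as part of the physical examination (footnote to Table 1: "Physical examination includes body weight, blood pressure, heart rate, edema, pulmonary rale, before and after hemodialysis session"), done once at baseline and then repeatedly: "Physical examination and urine volume collection will be performed every 2 months".
- Study design runs this "with a planned minimum 36 months follow-up period".

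The hypothesis for the left ventricular endpoint is worded as a level, "lower left ventricular thickness and higher left ventricular ejection fraction". The article does not say whether the t-test is applied to a follow-up level, a change from baseline or a per-patient average, or at which visit.

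**The concern.** A named test is a choice and not a detail left open, and this one does not match the data collected. A grouped t-test takes one number per patient and adjusts for nothing. Time enters only through trends within each arm, and these do not compare the randomised arms. The patient's own baseline is usually the strongest predictor of later blood pressure or wall thickness. Leaving it out of the between-arm model, or using it only through a change score, gives a wider confidence interval than the same data could give. At stake is the precision of the left ventricular and blood pressure comparisons. Validity under randomisation is not at stake, and nor is the primary endpoint.

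**Working it through.** **Inputs from the article.** Follow-up of at least 36 months; echocardiography every 12 months (36/12 = 3 follow-up values); blood pressure every 2 months (36/2 = 18 follow-up values); expected 3-year mortality 30%; loss to follow-up 20%; planned total 1354, allocated 1:1.

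**Input assumed.** The correlation r between baseline and follow-up is not given. I use 0.5 to 0.7 as the main range and 0.3 to 0.8 as the wider one, with equal variances at all visits.

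**The plan's own figure.** The article gives no standard deviation, effect size or power for these endpoints. Its only sample size is for the composite. That reproduces: 40% versus 32%, two-sided 5%, 80% power and pooled variance give 564 per arm, 1128 in all, and 1128 × 1.2 = 1354. It serves here only for head counts.

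**Variance of the arm difference, one follow-up visit** (t-test on the follow-up level = 1):

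- t-test on change from baseline: 2(1 − r)
- baseline-adjusted model: 1 − r²
- adjusted relative to change score: (1 − r²) / [2(1 − r)] = (1 + r)/2

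| r | Adjusted vs level | Cut | Adjusted vs change | Cut |
|---|---|---|---|---|
| 0.3 | 0.91 | 9% | 0.65 | 35% |
| 0.5 | 0.75 | 25% | 0.75 | 25% |
| 0.7 | 0.51 | 49% | 0.85 | 15% |
| 0.8 | 0.36 | 64% | 0.90 | 10% |

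Over r = 0.5 to 0.7 the adjusted variance is thus 0.75 to 0.51 of the level-based variance. The cut is 25% at the lower end and 1 − 0.51 = 49% at the upper end. This equals 1/0.75 = 1.33 to 1/0.51 = 1.96 times the sample size. Against a change-score test the cut is 25% down to 15%, or 1.33 down to 1/0.85 = 1.18 times.

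**Repeated visits.** With k follow-ups, equal correlation r between all visits and no missing data, the baseline-adjusted comparison of follow-up averages has relative variance [1 + (k − 1)r]/k − r².

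- k = 3: 0.417 at r = 0.5; 0.310 at r = 0.7
- k = 18: 0.278 at r = 0.5; 0.227 at r = 0.7

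These apply to an average over follow-up. For a contrast at one named visit with complete data, the gain is essentially that of baseline adjustment alone; the other visits then help through patients who missed that visit.

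**In units of detectable difference.** Removing 30% deaths leaves 1354 × 0.70 ≈ 948. Removing 20% of those leaves about 758 (56%), or 379 per arm. At 80% power and two-sided 5%, the detectable difference is (1.960 + 0.842) × √(2/379) = 0.204 SD for a t-test on month-36 levels. With baseline adjustment it is 0.204 × √0.75 = 0.176 SD at r = 0.5 and 0.204 × √0.51 = 0.145 SD at r = 0.7.

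None of these figures is applied to antihypertensive medication, which the article does not define as a continuous variable.

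**The case against.** The strongest reply is that the article never says baseline is ignored. A t-test on change from baseline is compatible with its wording, and scale and visit are details that a condensed article may leave to the analysis plan. This stands in part: the silence on scale and visit is no fault in itself, and the larger variance cut cannot be presented as an established loss. But the change-score reading shrinks the gain to 15% to 25% and does not remove it, because (1 + r)/2 is below 1 for any r below 1.

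It is also fair that the t-test is a valid between-arm test under randomisation apart from deaths and missing data, that no power is claimed for these endpoints, and that about 0.20 SD is detectable even so. All of this stands, and it limits the point to efficiency.

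Two stronger readings are tempting and not supported.

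- A reader might infer that the plan commits to a biased survivors-only comparison at month 36, which a mixed model would cure. The article names no such visit. Wall thickness and blood pressure cannot be measured after death under any method, and a mixed model on available visits does not by itself settle truncation by death. In an illustrative simulation (assumed mortality 30% versus 24%, no true effect on wall thickness, odds ratio of death 1.28 to 2.23 per SD of thickness), the spurious difference among survivors was 0.015 to 0.041 SD, against the BCM arm and small beside 0.204 SD.
- A reader might infer that benefit will be claimed from within-arm trends. The article makes the between-arm test the comparison and adds the trends; nothing in it rests an efficacy conclusion on them.

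**Conclusion.** The point holds as an inefficiency in the secondary endpoints. The article fixes a covariate-free between-arm test, and states no between-arm use of the repeated visits, where a baseline and several follow-up values are already scheduled. At an assumed r of 0.5 to 0.7, baseline adjustment would cut the variance by 25% to about half (1 − 0.51 = 49%, leaving a factor of 0.51) if levels are tested, or by 25% down to 15% if changes are tested, with more available from the repeated visits. The direction holds for any r between 0 and 1; the size depends on r and on the scale tested, neither of which the article gives. The primary analysis is not affected, and the material does not support a claim of material survivor bias or of misleading within-arm inference.

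**What to change.** Replace the grouped t-test for left ventricular measures and blood pressure with a linear mixed model on all available visits, with baseline value, arm, visit and arm-by-visit as terms. Report the between-arm difference with its confidence interval at a named visit, for example 36 months. Define the medication endpoint, for example as number of antihypertensive drugs, and analyse it with a count or ordinal model of the same structure. Keep within-arm trends as description only.

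Because about 30% are expected to die by three years, state how deaths are handled in these endpoints and say plainly that the model does not by itself resolve truncation by death. It should not be described as removing survivor bias.

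The cost is a change of wording and slightly more analysis work. No extra measurements, visits or patients are needed.

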**Methods:**

This is a multicenter, prospective, randomized, controlled trial. More than 1300 participants from 16 clinical sites will be included in the study. The enrolment period will last 6 months, and minimum length of follow-up will be 36 months. MHD patients aged between 18 years and 80 years who have been on MHD for at least 3 months and meet eligibility criteria will be invited to participate in the study. Participants will be randomized to BIA arm or control arm in a 1:1 ratio. A portable whole body bioimpedance spectroscopy device (BCM—Fresenius Medical Care D GmbH) will be used for BIA measurement at baseline for both arms of the study. In the BIA arm, additional BCM measurements will be performed every 2 months. The primary intent-to-treat analysis will compare outcomes for a composite endpoint of death, acute myocardial infarction, stroke or incident peripheral arterial occlusive disease between groups. Secondary endpoints will include left ventricular wall thickness, blood pressure, medications, and incidence and length of hospitalization.

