#### Secondary objectives

Secondary objectives are to compare the following indices between BCM arm and control arm: (1) left ventricular thickness and left ventricular ejection fraction, (2) Pre-HD and post-HD blood pressure, (3) anti-hypertensive medication, (4) hospitalization rate.

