##### Hospitalization

Hospitalization will be recorded, including diagnosis leading to hospitalization, date of hospitalization, length of stay, and outcome.

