#### Sample size calculation

Literature search failed to identify a study of similar design to this one. In an observational study by Wizemann et al.
[1] of 269 MHD patients the patients were divided into hypervolemic group if their ECF was 15% higher than normal or normohydrated group if less than 15%. The patients were followed for an average 3.5 years. There was 41% death in the hypervolemic group, and 30% death in normohydrated group. Relative risk of death was 36.6% higher in hypervolemic group than in the other.

According to data from Beijing Hemodialysis Quality Control and Improvement Center, the annual mortality rate of Beijing MHD patients is around 10%, it is estimated that 3 year mortality to be 30%. It is also estimated that the rate of composite endpoint within 3 year period of time is 40%. We make an assumption that BCM guided fluid management will reduce the 3-year composite endpoint rate from 40% to 32% (20% relative risk reduction). To reach statistical significance with α < 0.05 and 1-β > 80%, the sample size required is 1128. Allowing for a 20% loss-to-follow-up, the total sample size planned is 1354.

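### Hospitalization rate is to be compared by Poisson regression with no provision for overdispersion; if repeat admissions are counted and risk varies between patients, type I error exceeds 5%

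*Protocol article*

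**What the plan says.** Hospitalization is the last of the four secondary objectives (Secondary objectives: "4) hospitalization rate"). It returns as a directional secondary hypothesis (Study hypotheses: "4) lower hospitalization rate"). The analysis is one sentence under Secondary endpoint: the "incident rate of hospitalization will be compared between BCM arm and control arm using general Linear Model with Poisson regression". That sentence names no variance estimator, dispersion term or alternative model.

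On the data, a footnote to the schedule under Data collection says: "Any new clinical event throughout the study period will be recorded, including hospitalization". The Hospitalization paragraph adds: "Hospitalization will be recorded, including diagnosis leading to hospitalization, date of hospitalization, length of stay, and outcome". The abstract states that the "minimum length of follow-up will be 36 months". Nothing limits the analysis to a patient's first admission.

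**The concern.** Poisson regression with its default variance takes the variance of each patient's admission count to equal its mean. That holds if all patients with the same follow-up and covariates share one admission rate. It fails once some patients are more prone to admission than others, because repeat admissions then cluster in those patients.

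The article itself gives reason to expect such differences. Entry is open from age 18 to 80 and to any dialysis vintage from 3 months, at 16 sites that keep their own standard practice. The Cox model for death is adjusted for age, vintage, cause of ESRD, comorbidity, hypertension and hsCRP because these may alter risk. The hospitalization sentence lists no covariates.

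At stake are the confidence interval and p-value for one of the four secondary hypotheses. A chance difference in either direction would be called significant too often.

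**Working it through.** **The plan's own figures.** The article gives no rate, dispersion, power or significance level for hospitalization, so there is no figure to reproduce for this endpoint. Its primary sample size is used only to fix the setting: "To reach statistical significance with α < 0.05 and 1-β > 80%, the sample size required is 1128". For 40% against 32%, two-sided α = 0.05 and 80% power:

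n per arm = [1.960 × √(2 × 0.36 × 0.64) + 0.842 × √(0.40 × 0.60 + 0.32 × 0.68)]² / 0.08² = (1.330 + 0.569)² / 0.0064 ≈ 564, so 1128 in total.

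This matches exactly, and a one-sided test would give 890. A two-sided 5% level is therefore the working convention. The planned total of 1354 gives 677 per arm.

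**Formulas.** Suppose each patient's rate follows a gamma distribution, so that counts are negative binomial with mean μ and dispersion k.

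- Variance = μ + kμ², so variance/mean φ = 1 + kμ.
- The model-based Poisson standard error is too small by the factor √φ.
- True two-sided type I error = 2 × [1 − Φ(1.96/√φ)].

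**Assumed inputs (not in the documents).** μ = 2 to 4 admissions per patient over 3 years; k = 0.5 to 1.

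| μ | k | φ | √φ | Type I error |
|---|---|---|---|---|
| any | 0 | 1.0 | 1.00 | 5.0% |
| 2 | 0.5 | 2.0 | 1.41 | 16.6% |
| 2 | 1 | 3.0 | 1.73 | 25.8% |
| 3 | 0.5 | 2.5 | 1.58 | 21.5% |
| 3 | 1 | 4.0 | 2.00 | 32.7% |
| 4 | 0.5 | 3.0 | 1.73 | 25.8% |
| 4 | 1 | 5.0 | 2.24 | 38.1% |

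By symmetry about half of each figure favours the BCM arm: roughly 8% to 19%, against a nominal 2.5%.

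**In terms of the rate ratio.** Take μ = 3 and, for simplicity, full 3-year follow-up for 677 patients per arm, so 2031 admissions per arm. The Poisson standard error of the log rate ratio is √(2/2031) = 0.031, and an observed ratio of exp(−1.96 × 0.031) ≈ 0.94 would be called significant. With k = 0.5 the true standard error is 0.031 × 1.58 = 0.050 and the threshold is about 0.91. With k = 1 they are 0.063 and about 0.88.

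**Check by simulation with unequal follow-up.** The setting was 677 per arm, no treatment effect, exit at 0.105 per year (about the article's 10% annual mortality) capped at 3 years, and 4000 runs per scenario. At 1 admission per patient-year:

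| k | Model-based Poisson | Robust (sandwich) | Pearson-scaled |
|---|---|---|---|
| 0 | 5.2% | 5.3% | 5.3% |
| 0.25 | 13.7% | 5.2% | 5.7% |
| 0.5 | 21.5% | 5.4% | 6.0% |
| 1 | 32.3% | 5.0% | 5.6% |

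Over rates of 0.5 to 1.5 per year and k from 0.25 to 2, the model-based test rejected 8.4% to 53% of the time, the robust test 4.4% to 5.5%, and the Pearson-scaled test 4.7% to 6.4%. Unequal follow-up did no harm once person-time was in the model; the excess came from variation between patients.

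**The case against.** The strongest reply is that the article names a model family and is silent on the variance. Poisson regression with robust or scaled standard errors is still Poisson regression, and a condensed article may leave that choice to an analysis plan that is not shown. This stands in part: the text does not exclude a robust variance, so a reader should not infer that the default variance is settled. But the model is a stated choice rather than an omission, and an analyst who follows the sentence with default settings gets the invalid test.

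Second, both conditions are inferred. The article says that admissions are recorded throughout, not outright that every one enters the model, and it gives no distribution of admissions. That a few patients account for most admissions would be an assumption. This stands, and the point is conditional for that reason.

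Four stronger readings should be resisted.

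- A reader might infer that false positives are likely. In the main range the error is 17% to 38%: well above nominal, but under one half.
- A reader might infer a bias towards the BCM arm. Standard errors that are too small inflate rejection equally in both directions.
- A reader might infer that person-time is ignored. The article speaks of an incident rate and records the dates of admission and death, so events over time at risk are the ordinary reading.
- A reader might count the absence of covariates as an error. Randomization does not require them for this comparison.

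**Conclusion.** The point holds in conditional form. The stated method makes no provision for extra-Poisson variation in an endpoint for which repeat admissions are the natural reading and differences in risk between patients are to be expected. If all admissions count and the model-based variance is used, the type I error exceeds 5% whenever such differences exist.

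The direction of the error is firm; its size is not. The range of 17% to 38% depends wholly on the assumed mean of 2 to 4 admissions and dispersion of 0.5 to 1. Weaker variation (k = 0.25 at 1 admission per year) still gives about 14%, and none gives about 5%.

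The consequence is limited. Hospitalization is a secondary endpoint, does not drive the sample size, and is not named as a ground for stopping at the interim analyses. The correction should be made, but the primary conclusion does not depend on it.

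**What to change.** Replace the sentence under Secondary endpoint with one that says:

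- all admissions per patient during follow-up are counted;
- the arms are compared by negative binomial regression, or by Poisson regression with robust (sandwich) standard errors, with log follow-up time as offset;
- the rate ratio is reported with its 95% confidence interval.

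The offset probably only makes explicit what is already meant. The same edit can correct the name of the model class: Poisson regression is a generalized linear model, not a general linear model.

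The cost is a sentence or two. No new data, visits or patients are needed. Intervals widen, by a factor of 1.4 to 2.2 on the log scale under the assumptions above, so a modest true difference is less likely to reach significance. That loss reflects the information actually in the data. If there is no overdispersion, the robust version gives nearly the same result as the default.
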